#### Assessment of infection

A third person with adequate clinical acumen independent to the project will assess the post-CS infection to reduce any potential bias, for example, the obstetrics and gynaecology consultant on call and obstetrics and gynaecology registrar.

### Participant timeline {13}

The study flowchart and participant timeline are presented in Figs. 1 and 2, respectively.

**Fig. 1 Fig1:**
[figure not shown]
Flow chart demonstrating participant enrolment, randomisation, intervention and follow-up schedule

**Fig. 2 Fig2:**
[figure not shown]
Standard Protocol Items: Recommendations for Interventional Trials (SPIRIT) table of enrolment, intervention and assessments

### Sample size {14}

We assume that the interventions will improve the rate of infection including post-operative infective complications (within 28 days post-CS) by 50% compared to the control. Thus, for sample size estimation in this study, we set *P*_1_ = 8% (as per overall prevalence of post-CS infection range 3–15%), *P*_2_ = 4%, significance level = 5% and the study power = 80%.

Therefore,
$$ n\ge {\left(\frac{Z_{\alpha }+{Z}_{\beta }}{\mathrm{ES}}\right)}^2 $$$$ \mathrm{ES}=\frac{P_1-{P}_2}{\sqrt{P_1\left(1-{P}_1\right)}} $$

*n* ≥ 361

Here, *Z*_*α*_ = 1.96, *Z*_*β*_ = 0.84, *P*_1_ = 0.08, *P*_2_ = 0.04 and *P*_1_ − *P*_2_ = 0.04.

Considering 10% dropout, the study will require recruiting approximately 396 participants for all the groups (*n* = 132 in each group) over a period of 16 months to adequately test the assumption.

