## Introduction

### Background and rationale {6a}

Caesarean section (CS) is one of the methods of operative delivery in childbirth, and its rate has increased internationally over the last 3 decades for various reasons. According to the Australian Institute of Health and Welfare, the CS rate in Australia was 34% in 2016 [1]. Similar to any other surgical procedure, CS has morbidity in the form of infections, which include endometritis in addition to surgical site infection (SSI). This is a matter of concern as it has been reported that CS can have ten times higher risk of infections than that of vaginal delivery [2]. Furthermore, higher rates of infection have been identified in women with ruptured membranes and in women who undergo a CS in labour [3]. Such infections cause additional burden not only to the mother herself, but also to the newborn and her family as a whole. It also increases the risk of hospital readmissions and cost to health care systems across the world [4]. Olsen et al. demonstrated that wound infection and endometritis may incur an additional cost of US $4200 and US $4500 to the health systems, respectively [5]. Evidence favours the use of prophylactic antibiotics for CS to reduce post-operative infections by 60–70%, as well as the cost and duration of hospitalisation [6–8]. However, there are debates regarding single versus multiple doses, routes and timing of antibiotic use, type of antibiotics and duration. To reduce the rate of post-CS infections further, different antiseptics have been practised inconsistently for skin preparation and vaginal toileting. It has been demonstrated that vaginal preparation with povidone iodine or chlorhexidine solution compared to saline or not cleansing immediately before CS probably reduces the risk of post-CS infection [3]. However, a Cochrane review suggests no clear evidence favouring the use of chlorhexidine solution before surgery over other washing products to prevent SSI [9], while another Cochrane review reported that use of either chlorhexidine or povidone iodine before CS did not make any or might make little difference to the SSI or endometritis [2]. On the other hand, the World Health Organization (WHO) recommends the use of povidone iodine for vaginal cleansing immediately before CS to reduce maternal infection morbidities [10]. This recommendation is further emphasised in a recent systematic review and network meta-analysis by Roeckner et al. which reported that the use of 1% povidone iodine for pre-surgical vaginal irrigation among women who underwent CS had the most beneficial outcomes in the reduction of fever, wound infections and endometritis [11]. Despite the above measures, SSI incidence ranges from 3 to 15% [12], perhaps due to the variability of practices and individual preferences to one antiseptic agent over the other. Given the current limited data, it is imperative to identify the best evidence-based practice for uniform use of antiseptic agents for vaginal toileting to reduce post-CS infections or complications and to standardise their practice in a regional Australian hospital for enhanced recovery after caesarean delivery (ERAs).

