
### Objectives {7}

#### Hypothesis

H_1_: In a blinded randomised controlled clinical trial, using either chlorhexidine or povidone iodine for vaginal irrigation prior to CS will reduce post-operative infection outcomes by 50% when compared to no vaginal irrigation.

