### Outcomes {12}

#### Primary outcome

The primary outcome is endometritis: defined as tympanic temperature > 38 °C with uterine tenderness and/or foul-smelling vaginal discharge within 28 days of post-CS.

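### The sample size is planned on an 8% rate of overall post-caesarean infection, but the primary outcome is endometritis alone, so the stated 80% power does not apply to it

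*Protocol article*

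**What the plan says.** **Sample size {14}.** The section assumes that "the interventions will improve the rate of infection including post-operative infective complications (within 28 days post-CS) by 50% compared to the control". It sets P1 = 8% and P2 = 4%, with "significance level = 5" per cent and "the study power = 80" per cent. The 8% is justified "as per overall prevalence of post-CS infection range 3–15" per cent. The result is n ≥ 361, raised to about 396 (132 per group) for 10% dropout.

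**Primary outcome.** "The primary outcome is endometritis", defined as a tympanic temperature above 38 °C together with uterine tenderness, foul-smelling discharge or both, within 28 days. Fever, wound infection and readmission with infection are separate secondary outcomes.

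**Background and rationale {6a}.** "SSI incidence ranges from 3 to 15" per cent. This is the same range, here given for SSI. The opening of that section names endometritis as a further kind of infection alongside SSI.

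**Hypothesis.** Either antiseptic "will reduce post-operative infection outcomes by 50% when compared to no vaginal irrigation". The Discussion repeats the 50% reduction for infection in general.

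No endometritis rate appears anywhere in the article, and no sentence ties the 8% to endometritis.

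**The concern.** A power statement holds only for the outcome whose event rate went into it. Here the rate and the assumed reduction describe infection in general, while the trial's main conclusion will rest on endometritis. Nobody reading the article can tell what chance the trial has of detecting a halving of its own primary outcome.

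The consequence is practical. If endometritis is uncommon, each arm will have only a handful of events. A non-significant primary result would then say little, but beside a stated power of 80% it could be taken as evidence that vaginal cleansing does not work.

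**Working it through.** **1. Reproduce the plan's figure.** Inputs from Sample size {14}: P1 = 0.08, P2 = 0.04, Zα = 1.96, Zβ = 0.84.

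- ES = (0.08 − 0.04) / √(0.08 × 0.92) = 0.1474
- n = (2.80 / 0.1474)² = 360.6, so 361, as stated
- With 10% added, 361 × 1.10 = 397, close to the stated 396

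The figure follows from the 8%. What remains is which outcome the 8% describes.

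**2. Two readings of the 8%.**

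- *All post-caesarean infection* (wording of the Sample size section). Endometritis is then one component, and its rate is at most 8%.
- *SSI* (wording of the Background). Endometritis is then a different infection, and the 8% neither estimates nor bounds its rate.

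The article does not settle which is meant. On neither reading is 8% shown to be the rate of the primary outcome.

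**3. Effect of the rate alone, in the plan's own formula.** The control rates below 8% are my assumptions; the 50% reduction is kept. n = 7.84 × P1(1 − P1) / (P1/2)².

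| Control rate | n by the plan's formula |
|---|---|
| 8% (plan) | 361 |
| 5% (assumed) | 7.84 × 0.0475 / 0.000625 = 596 |
| 3% (assumed) | 7.84 × 0.0291 / 0.000225 = 1,014 |
| 2% (assumed) | 7.84 × 0.0196 / 0.0001 = 1,537 |

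**4. Power at the planned size.** Evaluable women per arm: 396 × 0.90 / 3 = 118.8, taken as 119. The comparison is one antiseptic against control, two-sided 5%, normal approximation with both tails counted. With d = P1 − P2 and p̄ the mean of the two rates, the upper-tail part is Φ[(d − 1.96·SE₀) / SE₁], where SE₀ = √(2p̄(1 − p̄)/119) and SE₁ = √((P1(1 − P1) + P2(1 − P2))/119).

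At 8% v 4%: SE₀ = 0.0308 and SE₁ = 0.0307, so Φ(−0.66) is about 0.25.

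| Control v treated | Expected events per arm | Power |
|---|---|---|
| 8% v 4% (plan) | 9.5 v 4.8 | about 25% |
| 5% v 2.5% (assumed) | 6.0 v 3.0 | about 17% |
| 3% v 1.5% (assumed) | 3.6 v 1.8 | about 12% |
| 2% v 1% (assumed) | 2.4 v 1.2 | about 10% |

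The Abstract and Discussion give 125 per group instead of 132. With all 125 analysed, power at 8% v 4% is about 26%, so that discrepancy does not matter here.

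**5. Separate the two causes.** The plan's formula has one-sample form, and its n is spread over three arms. The usual two-group formula at 8% v 4% gives 7.84 × (0.0736 + 0.0384) / 0.0016 = 549 per arm, against 119 available. The fall from 80% to about 25% comes from that and would be there even if 8% were the endometritis rate. Only the step from about 25% downwards belongs to this point, and it depends on the assumed rates.

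**The case against.** **The shortfall is mostly another error.** This stands. Step 5 assigns the drop from 80% to 25% to the formula. A reader who sees 10–17% beside the stated 80% might put the whole gap down to the choice of endpoint, and that would be wrong.

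**Nothing shows that endometritis is rarer than 8%.** This also stands. A reader might infer that the planning rate is too high. That follows only if the 8% covers all infection, and even then the bound is at most 8%, not strictly below it. If it is an SSI rate, there is no ceiling, and the Discussion describes a population with many comorbidities and high BMI. The supportable statement is that 8% is not shown to be the endometritis rate. Equally, nothing in the article breaks the 3–15% range down, so it cannot be said that wound infection or readmission accounts for most of it.

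**The hypothesis may pool the antiseptics.** It refers to either agent against no irrigation. With 240 treated against 120 controls, power is about 37% at 8%, 26% at 5%, 18% at 3% and 15% at 2%. The figures improve but the mismatch is unchanged.

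**Endometritis does address the hypothesis.** The hypothesis speaks of infection outcomes in the plural, and the Abstract says that infection is measured by the primary and secondary outcomes together. It would therefore be too strong to say that the primary outcome fails to answer the hypothesis; it answers part of it. This does not supply the missing rate.

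**Conclusion.** The point holds in this form: the planning rates, 8% v 4%, describe overall post-caesarean infection (or SSI, by the Background), the primary outcome is endometritis alone, and the article gives no endometritis rate. The stated 80% power therefore does not apply to the primary outcome. That conclusion needs no assumption beyond the text.

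Its size is not determined by the document. On assumed control rates of 5%, 3% and 2%, with a halving and 119 evaluable per arm, power is about 17%, 12% and 10%, against about 25% at the plan's own 8%. These are illustrations, not estimates of the trial's power.

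**What to change.** 1. Keep endometritis as the primary outcome. Replace P1 and P2 with a sourced endometritis-specific control rate and the reduction expected for it, and restate the power or the detectable difference actually achieved at the planned size. Do this with a two-group formula, so that the separate formula error is not carried over.
2. State that 8% v 4% concerns overall infection, and say whether the 3–15% range refers to SSI or to all post-caesarean infection.
3. Report overall infection within 28 days as a secondary outcome, with its components shown separately. The components are already being collected.

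The cost is a protocol amendment and a less favourable power statement; no new data are needed. Planned recruitment ended in December 2021, before the article appeared in March 2022. If recruitment is complete, the restated power and the mismatch should still be disclosed with the results.

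Making a composite infection outcome primary is an option only if it is decided before any outcome data are seen by arm and is declared as an amendment. Only participants are blinded and the treating team opens the allocation, so a late change invites the suspicion of outcome switching. Nor does it restore power by itself: at 8% v 4% power is still about 25%.

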### Trial design {8}

This will be a single-centre, three-arm, single-blind, randomised controlled trial. A total of 396 eligible patients will be randomised in a 1:1:1 ratio to receive pre-operative vaginal cleansing with 1% povidone iodine or chlorhexidine or no toileting (control) immediately prior to CS.

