## Statistical methods

### Statistical methods for primary and secondary outcomes {20a}

Baseline characteristics of participants including demographic characteristics, morbidity information with severity, current medication/management and satisfaction towards the current management will be compared using the *t*-test or and *χ*^2^ tests for categorical variables to assess the success of the randomisation. Summary statistics will be presented for all three groups’ infection information. BMI will be calculated using the weight and height of the participants. If required, the analysis will be performed following the ‘intention-to-treat’ analysis method. Primary and secondary outcomes will be compared using ANOVA. Where appropriate, logistic regression analyses will be used to compare the outcomes separately for interventions versus the control group. All data will be entered in MS Excel, and all statistical analyses will be performed using the STATA 11.0 statistical package.

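### The sample size uses a one-sample formula and spreads its answer over three arms; the claimed 80% power is about 25% for each antiseptic-versus-control comparison

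*Protocol article*

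**What the plan says.** Sample size {14} assumes that the interventions lower the infection rate "by 50% compared to the control", from P1 = 8% to P2 = 4%. It sets "significance level = 5% and the study power = 80" per cent, with Zα = 1.96 (so two-sided) and Zβ = 0.84. The formula is n ≥ ((Zα + Zβ)/ES)², with ES = (P1 − P2)/√(P1(1 − P1)), and the result is n ≥ 361. The section continues: "Considering 10% dropout, the study will require recruiting approximately 396 participants for all the groups". It gives 132 for each group and describes this as adequate for testing the assumption.

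Trial design {8} confirms that this figure is a total: "A total of 396 eligible patients will be randomised in a 1:1:1 ratio". Under Statistical methods {20a}, outcomes are compared across groups by ANOVA and, where appropriate, "logistic regression analyses will be used to compare the outcomes separately for interventions versus the control group". The hypothesis in Objectives {7} is that either antiseptic halves infection compared with no irrigation.

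**The concern.** The formula's only variance term is P1(1 − P1). It has no P2 term and no allowance for a second randomised group, so it treats the control rate as known without error. In this trial the control rate is estimated from a concurrent arm about as small as each active arm. That is the first error. The second is that the one-group answer becomes the total for three arms, leaving each with a third of it. Both errors push the number down, and they compound.

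The 80% figure is the trial's quantitative justification. If true power is far lower, a non-significant result says little about whether vaginal cleansing works. The protocol intends to build a uniform local guideline on these data and lists a low infection rate and a single site as limitations, but not low power. The protocol does not say that a null result would be read as no effect, but its 80% claim would invite that reading.

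**Working it through.** **Inputs (Sample size {14}, Trial design {8}).** P1 = 0.08, P2 = 0.04, two-sided 5% (1.96), 80% power (0.84), 132 randomised per arm, 10% dropout. Evaluable per arm: 132 × 0.9 = 118.8, about 119.

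**1. Reproducing the protocol's figure.**
- ES = 0.04/√(0.08 × 0.92) = 0.1474.
- n = (2.80/0.1474)² = 360.6, so 361. The printed formula and answer agree, so the origin of the number is not in doubt.
- Dropout: 361 × 1.1 = 397 and 361/0.9 = 401; the protocol's 396 equals 3 × 132. This small difference does not matter here.

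**2. What a two-arm comparison needs.**
- Unpooled variance: n per arm = 2.80² × (0.0736 + 0.0384)/0.04² = 548.8, so 549.
- Pooled variance under the null (mean rate 0.06): n per arm = [(1.96√(2 × 0.06 × 0.94) + 0.84√(0.0736 + 0.0384))/0.04]² = 551.5, so 552 (553 with unrounded normal quantiles).
- Three arms: 3 × 549 = 1,647 to 3 × 553 = 1,659 evaluable. With 10% dropout, 553/0.9 gives 615 per arm, or 1,845 randomised.
- The planned 119 is smaller than 552 by a factor of 552/119 = 4.6.

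**3. Power of the planned design, one antiseptic v control, 119 per arm.**
- Standard error under the null: √(0.06 × 0.94 × 2/119) = 0.03079.
- Standard error under the alternative: √(0.112/119) = 0.03068.
- z = (0.04 − 1.96 × 0.03079)/0.03068 = −0.663, so power = 25.4%.
- Exact enumeration at 119 per arm gives 25.8% for the chi-square test and about 16% for Fisher's test.

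**4. More favourable readings.**

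| Reading | Power for 8% v 4% |
|---|---|
| Pairwise, 132 per arm, no dropout | 27.6% |
| Pairwise, 120 per arm, one-sided | 37% |
| Both antiseptics pooled v control, 238 v 119 | 36.8% |
| Both antiseptics pooled v control, 264 v 132, no dropout | 39.7% |
| Three-group test, 119 to 132 per arm | 26% to 29% |
| Pairwise, if 361 were the size of each arm | 62% |

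For the pooled row at 238 v 119, the mean rate is (0.08 + 2 × 0.04)/3 = 0.0533. The standard errors are √(0.0533 × 0.9467 × (1/119 + 1/238)) = 0.02523 and √(0.0736/119 + 0.0384/238) = 0.02793. Then z = (0.04 − 1.96 × 0.02523)/0.02793 = −0.338.

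**5. Sensitivity to the control rate.** Over the protocol's quoted range of 3% to 15%, with a 50% reduction, pairwise power at 120 per arm runs from about 12% to about 45%.

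**6. What 119 per arm could detect.** Starting from 8%, exact chi-square power is 83% if the active rate is 0.8% and 79% if it is 1.0%. Reaching 80% thus needs an active rate just under 1%, a reduction of nearly 90% (0.07/0.08 = 87.5% at 1.0%).

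**The case against.** Several points can be made for the plan.

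- **Main test.** The planned comparison is ANOVA, with separate regressions only where appropriate, so a pairwise figure may not describe the main test. That is fair, but the three-group test has 26% to 29% power, so the conclusion does not change.
- **Pooling.** The hypothesis speaks of either antiseptic, which might mean the two active arms combined. No section says they are pooled for the power calculation, and pooling reaches only 37% to 40%.
- **Two chances of success.** Missing the effect three times in four applies to each comparison; the chance that at least one antiseptic reaches significance is higher. It cannot exceed twice the single-comparison power, 2 × 25.4% = 50.8%, and that is before any multiplicity correction.
- **Assumed rates.** The 25% depends on 8% and 4%, which describe post-caesarean infection overall, whereas the primary outcome is endometritis alone. The figure should be labelled as holding under the protocol's rates. A lower endometritis rate would reduce power further.
- **Capacity.** Recruitment {15} gives 25% of about 1,200 deliveries a year, or 300 caesareans, hence about 400 in 16 months. The sample may be all the site can provide. That explains the number but does not support the power claim.

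A separate analysis plan could not repair this, because the formula, its result and the power claim are all printed in the protocol article. The abstract and Discussion give 125 per group, where pairwise power is 26.4%, so that discrepancy is immaterial here.

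**Conclusion.** The concern holds. The calculation is a one-sample formula whose answer is divided among three arms, and the stated 80% power is wrong. Under the protocol's own rates (8% v 4%, two-sided 5%, 10% dropout), power is about 25% for each antiseptic against control, and no reading of the text reaches 80%. The required number per arm is understated more than fourfold. The size of the shortfall depends on the control rate, but pairwise power stays below 50% across the whole 3% to 15% range that the protocol quotes. This must be corrected, because the protocol presents the trial as adequately powered when it is not.

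**What to change.** In Sample size {14}:

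- Replace the formula with a two-proportion calculation that includes the variance of both arms. Report its result: about 550 evaluable per arm for 8% v 4% at two-sided 5% and 80% power.
- State the power of the trial as planned. For example: with 132 randomised and about 119 evaluable per arm, power to detect 8% v 4% is about 25% for each antiseptic-control comparison and about 37% for both antiseptics combined against control.
- Delete the claim that the sample is adequate to test the assumption, and name low power as a limitation in the Discussion.

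In Statistical methods {20a}, state that results will be reported as risk ratios with 95% confidence intervals and that a non-significant difference will not be read as no effect.

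If the team wants one confirmatory contrast, antiseptics combined against control is the best-powered candidate, with the individual arms reported as estimates. This is optional: it sits less well with the aim of finding the better antiseptic, and it is still underpowered.

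The cost is protocol wording and a less favourable stated power; no extra patients are needed. Reaching 80% would take about 1,845 randomised, more than six years of the site's caesareans at 300 a year (1,845/300 = 6.15) even if every woman took part.

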### Recruitment {15}

Participants will be recruited from the clinical setting. All expecting pregnant women attending Goulburn Valley Health Obstetrics and Gynaecology Department will be viewed as potential participants and invited to take part in the study; although this study concentrates purely on CS delivery (both elective and emergency) and not vaginal delivery, emergency CS delivery with intended vaginal delivery is mostly unpredictable. Considering CS deliveries comprise 25% of a total of approximately 1200 deliveries annually at Goulburn Valley Health, it is expected that we will recruit the required number of participants to reach the target sample size in 16-month period. Strategies to achieve adequate participant recruitment include the invitation of all pregnant women to participate, as well as study awareness and familiarity among departmental staff.

## Assignment of interventions: allocation

### Sequence generation {16a}

After inclusion in the trial, each prospective CS patient will be assigned either into the intervention (1% povidone iodine or chlorhexidine) or control (no-irrigation) group by using a block randomisation technique. A permuted block of six will be used to randomise the patients. A third party not related to the study will generate the permuted blocks and allocate the treatment in sealed opaque envelopes.

